**Length of stay in hospital**	
**Death, if any**	

H: Postoperative hours, D: Postoperative days

### Study schedule

Enrolment period: 36 monthsFollow-up period: 2 monthsTotal duration of the study: 38 months

### Screening visit (day - 60 to day - 5 prior to randomization)

#### Visit 2 baseline (week 0/Day-1)

The baseline visit occur after the patient has signed the informed consent document. All baseline procedures and tests must be completed prior to randomization: review of eligibility criteria, blood chemistry and serum creatinine, health outcomes assessments.
Day 0: surgery and randomization - Operative period (Table 1)Postoperative period (Table 2)

### Statistical methods

The main objective is to study the potential effectiveness of the IPC regarding postoperative pulmonary and renal complications in the two arms during the first 8 days following surgery. As of other complications may occur before the occurrence of a pulmonary or renal complication, a Cox regression model for competing risks will be used to estimate and test the effect of PCI on the occurrence of a postoperative pulmonary complication [36]. The study will be conducted with an alpha risk of .05 for two-sided tests comparing the null hypothesis to the alternative (the risk of a pulmonary or renal complication differs between the two arms). Both arms will be considered to differ significantly if the null hypothesis is rejected.

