### Primay endpoint

The primary endpoint is the occurrence of a first pulmonary or renal complication during the 8-day postoperative period.

Pulmonary complications are defined as:
The necessity of prolonged artificial ventilation, i.e. no extubation before the 48-h following the surgeryThe need for a new ventilation (invasive or noninvasive) within 48-h following initial extubationThe occurrence of a moderate or severe acute respiratory failure, according to the Berlin definition [34].

Renal complication is defined as the occurrence of an acute kidney failure according to the RIFLE classification [19], as “injury”, “failure” or “loss” during the first postoperative week.

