### Secondary endpoints

The secondary endpoints are:
Need for new ventilation (invasive or noninvasive) 48 h after the arrest of initial ventilation, during a 21-day postoperative period.Renal failure occurring during a 21-day postoperative period according to the RIFLE classificationCardiac morbidity: daily serum troponin > 1.5 normal level (specific in each center) within the 48-h postoperative period.Cellular and tissue visceral impairment: daily serum D-lactate during the first 8-day postoperative period.Mortality at 60 days

This study is randomized in two arms on the day of surgery by drawing lots
Arm 1: patients with aortic clamping with preconditioningArm 2: patients with aortic clamping without preconditioning

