### Number of patients to be enrolled

The sample size is calculated taking into account an estimated risk of pulmonary and renal complications around 36% following OSR for TAAA in patients operated without PCI [6] and a postoperative mortality around 1% of the patients before the 8th day (observed in the selected centres). With the hypothesis of a corresponding risk in the PCI group around 15%, the randomization of 110 patients, with an allocation ratio of one to one, will detect a Hazard Ratio ≥ 2.75 between both arms with a power of 80% and an alpha risk of 5%.

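### The stated reason for the competing-risks model is other complications, but non-fatal ones do not preclude the primary event, and the sample size considers only death

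*Protocol article*

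**What the plan says.** Three sections of the protocol article bear on this point.

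- **Primary endpoint:** "The primary endpoint is the occurrence of a first pulmonary or renal complication during the 8-day postoperative period". The definition makes no exception for patients who first have some other complication.
- **Statistical methods:** "As of other complications may occur before the occurrence of a pulmonary or renal complication", and for that reason "a Cox regression model for competing risks will be used to estimate and test the effect of PCI" (the article writes PCI for IPC here). No other reason for the model is given. Death is not named, and the text does not say whether the model is cause-specific or subdistribution.
- **Number of patients to be enrolled:** the calculation takes "an estimated risk of pulmonary and renal complications around 36% following OSR for TAAA in patients operated without PCI" and "a postoperative mortality around 1% of the patients before the 8th day". Death is the only candidate competing event given a figure.

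The Secondary endpoints section also lists an early complication that is neither pulmonary nor renal: "daily serum troponin > 1.5 normal level (specific in each center) within the 48-h postoperative period".

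**The concern.** A competing event is one after which the event of interest can no longer occur. Death meets that definition. A raised troponin within 48 h does not, because the patient can still need renewed ventilation or develop kidney injury on day 3. The endpoint definition would count that event. A competing-risks analysis that ends the patient's chance of a primary event at the first other complication would not.

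Two things are at stake. First, events: only about 28 are expected, so each one lost matters. Second, bias. Cardiac complications are compared between arms as a secondary objective, so an effect of IPC on them is considered possible. If IPC changes how often other complications occur, the number of primary events removed differs by arm. If other complications and the primary event also share causes, as the article's systemic-inflammation rationale makes plausible, censoring at the other complication is informative even in a cause-specific model.

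**Working it through.** **Inputs from the documents.** Risk to day 8 is 36% control and 15% IPC. There are 55 patients per arm, the hazard ratio (control to IPC) is 2.75, alpha is two-sided 0.05, and mortality before day 8 is about 1%.

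**Inputs assumed.** The documents give no frequency for other complications and no effect of IPC on them. I use 20% and 30% in both arms, then 30% against 15% in each direction.

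**1. The plan's own figures.**
- Hazard ratio: ln(0.64)/ln(0.85) = 2.746, which matches 2.75.
- Expected events: 55 × (0.36 + 0.15) = 28.05.
- Power (Schoenfeld): Φ(ln 2.75 × √28.05 / 2 − 1.96) = 76.4%, or 76.0% after removing 1% of events for deaths.
- The stated 80% is not reproduced by this formula, which needs 31 events and about 122 patients. That is a separate matter. I use 76% as the baseline so that the comparison is like with like.

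**2. Method.** Take constant hazards over the 8 days, with the other complication independent of the primary event. For primary risk p and other-complication risk q, set λ = −ln(1−p) and μ = −ln(1−q). The probability that the primary event comes first is

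F = λ/(λ+μ) × [1 − (1−p)(1−q)].

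The subdistribution hazard ratio is approximated by ln(1−F_control)/ln(1−F_IPC), and events by 55 × (F_control + F_IPC). Here λ is 0.4463 for control and 0.1625 for IPC. For q = 15%, 20% and 30%, μ is 0.1625, 0.2231 and 0.3567.

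Worked example, 30% in control: F = 0.4463/0.8030 × (1 − 0.64 × 0.70) = 0.307. With 15% under IPC: F = 0.1625/0.3250 × (1 − 0.85 × 0.85) = 0.139. The ratio is ln(0.693)/ln(0.861) = 2.45.

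**3. Results under independence.**

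| Competing event, control / IPC | F control / IPC | Events | Subdistribution HR | Power |
|---|---|---|---|---|
| Death only, 1% / 1% | 0.358 / 0.149 | 27.9 | 2.74 | 76% |
| Other, 20% / 20% | 0.325 / 0.135 | 25.3 | 2.72 | 71% |
| Other, 30% / 30% | 0.307 / 0.127 | 23.8 | 2.70 | 68% |
| Other, 30% / 15% | 0.307 / 0.139 | 24.5 | 2.45 | 60% |
| Other, 15% / 30% | 0.334 / 0.127 | 25.4 | 3.00 | 79% |

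The cause-specific hazard ratio is λ_control/λ_IPC = 2.75 in every row. In that model only events are lost.

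**4. No true effect on the primary endpoint.** With 36% in both arms and other complications 30% against 15%, F is 0.307 and 0.334. The subdistribution ratio is ln(0.693)/ln(0.666) = 0.90. With 15% against 30% it is 1.11.

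**5. Correlated complications.** A simulation with a shared gamma frailty of variance 1 gives a loss of 14-27% of primary events when other complications are 20-30% in both arms. For 30% against 15%, the subdistribution ratio is 2.38 (power 54%) and the cause-specific ratio 2.68. For 15% against 30%, they are 3.36 and 3.07.

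**The case against.** The clause gives a motive for choosing a model. It is not a coding rule. No section lists competing events, says how an earlier non-fatal complication is handled, or stops follow-up at one. Table 2 schedules creatinine and blood gases daily to day 8 without such a stop. The English is rough, other complications could loosely include death, and the sample-size section points to death. Detailed competing-event definitions often sit in an analysis plan or full protocol, which are not shown.

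Much of this stands. A reader might infer that the trial will certainly discard these events. The article does not show that, and a missing list is not the finding. What remains is that the only reason given for the primary model is wrong as worded. An analysis plan that follows the sentence inherits the error, and one that uses death alone departs from it.

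A second stronger inference concerns size. A reader might equate 20-30% of patients having another complication with 20-30% of primary events being blocked. That gives 22.4 to 19.6 events and power of 64% to 57%. With 30% against 15%, it gives a hazard ratio of 2.13, power of 41% and a null ratio of about 0.79. It would require every other complication to come before the primary event, and nothing in the documents supports that. Nor do they support a fixed direction of bias against IPC.

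**Conclusion.** The point holds as an error in the stated basis of the primary analysis. The justification names events that do not preclude the primary event, and so conflicts with an endpoint that counts pulmonary and renal complications regardless of what preceded them and with a sample size that considers only death.

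The size is conditional on assumed rates. If the clause is applied literally, 20-30% other complications in both arms would cost about 3 to 4 of 28 expected events and about 5 to 8 percentage points of power. Bias in the hazard ratio depends on three things that the article leaves open: whether IPC changes other complications, how strongly they correlate with the primary event, and which competing-risks model is used. It can run either way. In the uneven scenarios under independence, the subdistribution ratio runs from 2.45 to 3.00 while the cause-specific ratio does not move. With death as the only competing event, the effect is negligible.

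**What to change.** In Statistical methods, replace the clause about other complications with: *Death before a first pulmonary or renal complication is the only competing event; patients with other non-fatal complications remain at risk and are followed for the primary endpoint to day 8.* This aligns the analysis with the endpoint definition and with the mortality figure in the sample-size section. The same edit should state whether the model is cause-specific or subdistribution, since the consequences differ.

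The cost is a sentence or two in the protocol, carried into the analysis plan. No extra data are needed, because the postoperative schedule in Table 2 already runs daily to day 8. The change should be made before outcome data are analysed by arm.

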### Number of patients to be enrolled

The sample size is calculated taking into account an estimated risk of pulmonary and renal complications around 36% following OSR for TAAA in patients operated without PCI [6] and a postoperative mortality around 1% of the patients before the 8th day (observed in the selected centres). With the hypothesis of a corresponding risk in the PCI group around 15%, the randomization of 110 patients, with an allocation ratio of one to one, will detect a Hazard Ratio ≥ 2.75 between both arms with a power of 80% and an alpha risk of 5%.

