## Background

Mortality rate after OSR for TAA is estimated between 4 and 15% [1, 2]. Pulmonary and renal complications can reach up to 50% and more [3, 4]. Compared to OSR for infrarenal abdominal aortic aneurysm (AAA), TAA requires repair of the visceral arteries with a supravisceral aortic cross-clamping often greater than 30 min. Following OSR for TAA, Serious lung damage reached 60% in large series [3, 5] and 40 to 50% in recent publications [6]. The hypothesis of a causal link between visceral ischemia and the occurrence of organ failure and particularly lung damage is the main focus of this study. Mesenteric ischemia reperfusion caused by aortic cross clamping above the celiac trunk and the superior mesenteric artery is involved in the onset of a systemic inflammatory response (SIRS) leading to multiple organ failure (MOF) [7–10]. Interestingly, distal perfusion of the aorta by a shunt reduces the onset of paraplegia, but increases the production of cytokines and complications associated with the inflammatory response [11, 12].

The main actors of the inflammatory response to ischemia-reperfusion are free radicals’ oxygen, polymorphonuclear neutrophil cells (PMN) and cytokines, all at the origin of the deleterious complications [13–15]. In particular, activity of neutrophils could be a key factor in remote lung injury [16, 17].

Beside remote lung injury, renal damage can be mainly attributed to direct effect of cross aortic clamping during TAA. Severe acute renal failure reaches 25% with dialysis required in 17% of patients [6] with an increased risk of death [18]. Wynn et al. reported that renal failure as defined in the RIFLE classification [19] was not associated with increased mortality [20]. According to Tshomba et al. [21] acute renal failure is often temporary. But even temporary, it is possible that acute renal failure observed in this context may later favour the onset of chronic renal failure [22].

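### The 36% control risk for the lung-or-kidney composite is not reconciled with the 40 to 50% lung damage cited from the same reference, and at 36% the stated 80% power is about 76%

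*Protocol article*

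**What the plan says.** All places are in the protocol article.

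- **Number of patients to be enrolled.** The control risk is "an estimated risk of pulmonary and renal complications around 36% following OSR for TAAA in patients operated without PCI [6"]. The section continues "With the hypothesis of a corresponding risk in the PCI group around 15"%, allows for "a postoperative mortality around 1% of the patients before the 8th day (observed in the selected centres"), and concludes that 110 patients randomised one to one "will detect a Hazard Ratio ≥ 2.75 between both arms with a power of 80% and an alpha risk of 5"%. (PCI here is the preconditioning abbreviated IPC elsewhere.) The Abstract repeats 36%, 55 per arm, 2.75 and 80%.
- **Primary endpoint.** "The primary endpoint is the occurrence of a first pulmonary or renal complication during the 8-day postoperative period". The pulmonary part is met by ventilation still needed at 48 hours, by renewed ventilation (noninvasive included) soon after extubation, or by moderate or severe respiratory failure on the Berlin criteria. The renal part starts at the injury grade of RIFLE.
- **Background.** "Serious lung damage reached 60% in large series [3, 5] and 40 to 50% in recent publications [6"], and "Severe acute renal failure reaches 25% with dialysis required in 17% of patients [6"].
- **Statistical methods.** "The study will be conducted with an alpha risk of .05 for two-sided tests".

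The article does not say how 36% was obtained from reference 6, or how it relates to the two Background figures.

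**The concern.** A patient with a lung complication already meets an endpoint that counts lung or kidney complications. With common definitions, window and patients, the composite is at least as frequent as its more frequent component. The planning rate of 36% lies below the 40 to 50% cited from the same source for one component.

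The 36% is the anchor of the design. With the hypothesised 15% it gives the hazard ratio of 2.75, and the two risks together set the expected number of events and so the power. If 36% is not the control risk of this endpoint, the statement of what 110 patients can detect does not describe this trial. A reader of a null result could not then tell whether the effect was absent or the planning rate was off.

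**Working it through.** **Inputs.** Control risk 36%, preconditioning risk 15%, 110 patients at 1:1, hazard ratio 2.75 and power 80% (sample-size section); two-sided 5% (Statistical methods); lung damage 40 to 50% and severe renal failure 25% (Background). The 1% mortality is ignored below; allowing for it raises the required number slightly.

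**1. The plan's hazard ratio.** Under proportional hazards, HR = ln(1 − 0.36) / ln(1 − 0.15) = (−0.4463) / (−0.1625) = 2.746. This matches 2.75.

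**2. The plan's sample size.** Schoenfeld events = 4 × (1.960 + 0.842)² / (ln 2.75)² = 4 × 7.849 / 1.0116² = 30.7, so 31. The mean risk is (0.36 + 0.15) / 2 = 0.255, so N = 31 / 0.255 = 121.6, i.e. 122 (123 with 1% deaths). Other two-sided methods give more: two proportions 134, Freedman 146. The 110 is not reproduced. Only one-sided variants come near it (two proportions 106, Freedman 111).

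**3. Power at 110, on the plan's own rates.** Events = 55 × (0.36 + 0.15) = 28.05. Power = Φ(½ × √28.05 × ln 2.75 − 1.960) = Φ(0.719) = 76%. A comparison of two proportions gives 72%.

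**4. What the Background figures would imply for the composite**, if they applied to this endpoint, window and population:
- full overlap of lung and renal events (lower bound): 40 to 50%;
- independence (an assumption): 1 − 0.60 × 0.75 = 55% to 1 − 0.50 × 0.75 = 62.5%;
- no overlap (upper bound): 65 to 75%.

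36% lies below all of these.

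**5. Effect on the design statement**, 55 per arm, two-sided 5%, Schoenfeld. Here pc and pt are the control and preconditioning risks, and events = 55 × (pc + pt).

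| pc | (a) HR fixed at 2.75: pt, events, power | (b) 21-point difference fixed: pt, HR, power | (c) HR detectable with 80% power |
|---|---|---|---|
| 36% | 15.0%, 28.0, 76% | 15%, 2.75, 76% | 2.90 |
| 40% | 17.0%, 31.3, 81% | 19%, 2.42, 71% | 2.72 |
| 50% | 22.3%, 39.8, 89% | 29%, 2.02, 64% | 2.39 |
| 60% | 28.3%, 48.6, 94% | 39%, 1.85, 62% | 2.18 |

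In (a), pt = 1 − (1 − pc)^(1/2.75). In (b), pt = pc − 0.21 and HR = ln(1 − pc) / ln(1 − pt). In (c), HR solves ½ × √events × ln HR = 1.960 + 0.842, with pt = 1 − (1 − pc)^(1/HR), so that the events change with the HR.

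If instead the 15% is kept, the implied HR rises to ln 0.60 / ln 0.85 = 3.14 at 40% and ln 0.50 / ln 0.85 = 4.27 at 50%.

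**The case against.** The rule that a composite is at least as frequent as its component needs the same event definition, window and patients. The Background gives none of these for its lung figure, uses upper-end wording, and speaks of publications in the plural. The trial counts specified events over 8 days, excludes emergencies and circulatory arrest, and admits some abdominal aneurysms with visceral reconstruction. A true composite risk of 36% is therefore possible, and reference 6 is not at hand to settle it. This stands, and it rules out a tempting stronger reading: that the planning rate is impossible on the article's own figures.

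The 55 to 62.5% range also needs independence, which the article's rationale of one shared ischemia-reperfusion mechanism makes doubtful. It is an illustration, not an estimate.

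A higher control risk raises power when the hazard ratio is fixed, so 36% could be called conservative. That holds only under that choice; with the 21-point difference kept, power falls.

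The shortfall to 76% comes from 110 patients under a two-sided test, not from 36% being too low. That is correct. It belongs here because the same sentence has to be recalculated.

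Finally, a condensed article may leave the derivation of a planning rate to the full protocol. But here the article prints both figures, credits them to one source, and leaves them in conflict. Nor does the endpoint look narrow: three pulmonary criteria, plus renal failure from the injury grade upward.

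**Conclusion.** The 36% and the 40 to 50% are inconsistent as written and unexplained. That 36% is wrong for this endpoint is not established.

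It also cannot be inferred that the trial has too much or too little power because of this discrepancy. From 40% to 50% control risk, power runs from 81% to 89% with the hazard ratio held at 2.75, and from 71% to 64% with the 21-point difference held. The direction depends on what the sponsor regards as the target effect.

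What holds whichever rate is right: the 2.75 agrees with 36% versus 15%, but 110 patients give about 28 events and about 76% power on those rates. The hazard ratio detectable with 80% power is about 2.90 at 36%, 2.72 at 40%, 2.39 at 50% and 2.18 at 60%. These results assume proportional hazards, the Schoenfeld approximation, full follow-up to day 8 and negligible competing mortality.

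**What to change.** In the section on the number of patients:

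1. State which event, time window and patients in reference 6 the 36% describes, and reconcile it with the 40 to 50% and 25% in the Background. If the definitions differ, say so in both places.
2. Use a control risk that matches the primary endpoint as defined.
3. Restate power for 110 patients at two-sided 5%, naming the method and what is held fixed: about 76% at 36% versus 15%; with hazard ratio 2.75, about 81% at 40% and 89% at 50%; with a 21-point difference, about 71% and 64%. Add the detectable hazard ratios from the last column of the table. Make the same change in the Abstract.

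The cost is a paragraph and one recalculation. Enrolment, treatment and endpoint need not change. The downside is that the stated power at 36% becomes less favourable.

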**Methods:**

The primary objective of the study is to evaluate the efficacy of IPC during OSR for TAA with respect to acute kidney injury (AKI) according to KDIGO and pneumonia/prolonged ventilation-time during the first 8 postoperative days. The secondary objectives are to compare both arms with respect to cardiac complications within 48 h, renal and pulmonary complications within 21 days and mortality at 60 days.

To assess the efficacy of IPC with respect to pulmonary and renal morbidity, a cox model for competing risks will be used. Assuming that the event occurs among 36% of the patients when no IPC is performed, the allocation of 55 patients to each arm should allow detecting a hazard ratio of at least 2.75 with a power of 80% when admitting 5% for an error of first kind. This means that 110 patients, enrolled in this multicenter study, may be randomised within 36 months of the first randomization.

Randomization will be performed to allocate patients either to surgery with preconditioning before aortic cross clamping (Arm 1) or to surgery without preconditioning before aortic cross clamping (Arm 2).

Randomization takes place during the intervention after intravenous injection of heparin, or after the start of femoral assistance. The procedure for IPC will be a supra-visceral thoracic aortic cross clamping for 5 min followed by an unclamping period of 5 min. This procedure will be repeated twice before starting thoracic aortic cross clamping needed to perform surgery.

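### With 55 patients per arm, risks of 36% and 15% and a two-sided 5% test, power for HR 2.75 is about 70–76%, not the stated 80%

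*Protocol article*

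**What the plan says.** The sample-size section (Number of patients to be enrolled) lists its inputs:

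- control risk: "an estimated risk of pulmonary and renal complications around 36% following OSR for TAAA in patients operated without PCI" (the article writes PCI there for ischemic preconditioning, elsewhere IPC);
- experimental risk: "With the hypothesis of a corresponding risk in the PCI group around 15" per cent;
- early deaths: "a postoperative mortality around 1% of the patients before the 8th day";
- size: "the randomization of 110 patients, with an allocation ratio of one to one".

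From these it concludes that the trial "will detect a Hazard Ratio ≥ 2.75 between both arms with a power of 80% and an alpha risk of 5" per cent. The Methods part of the abstract repeats the claim: "the allocation of 55 patients to each arm should allow detecting a hazard ratio of at least 2.75 with a power of 80" per cent.

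Neither place gives the sidedness. The Statistical methods section does: "The study will be conducted with an alpha risk of .05 for two-sided tests comparing the null hypothesis to the alternative". That section also names a Cox regression for competing risks as the primary analysis, over the first 8 days after surgery.

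**The concern.** The article prints every quantity needed to check its power claim: both risks, the hazard ratio, the number per arm, the significance level and, for the analysis, its sidedness. Put together, they do not give 80%.

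This calculation is the only justification offered for the sample size on the primary endpoint. If it is too optimistic, the chance of missing the planned effect is larger than readers are told. That effect is already large, with the risk cut by more than half. The Background reports conflicting results for preconditioning, so a non-significant result is a realistic outcome, and its meaning depends on a correct power figure.

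**Working it through.** **Inputs, all from the article.** Control risk 0.36, preconditioning risk 0.15, 55 per arm, HR 2.75, early mortality about 1% (sample-size section and abstract); two-sided alpha 0.05 (Statistical methods). Normal quantiles: 1.960 for two-sided 5%, 0.8416 for 80% power.

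**Step 1. The hazard ratio is reproduced.** Under proportional hazards, HR = ln(1 − 0.36)/ln(1 − 0.15) = (−0.4463)/(−0.1625) = 2.746, which rounds to the stated 2.75. The effect size is not in dispute.

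**Step 2. Expected events.** 55 × 0.36 + 55 × 0.15 = 19.8 + 8.25 = 28.05. The 1% mortality lowers this slightly, to about 27.9.

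**Step 3. Schoenfeld's formula (the most favourable of those tried).**
- Power = Φ(½ × √28.05 × ln 2.75 − 1.960) = Φ(2.679 − 1.960) = Φ(0.719) = 76.4%.
- Events needed for 80% = 4 × (1.960 + 0.8416)² / (ln 2.75)² = 30.7, so 31.
- Patients needed = 31 / 0.255 = 121.6, so about 122, where 0.255 is the average of the two risks.

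**Step 4. Freedman's formula.**
- Power = Φ(√28.05 × (2.75 − 1)/(2.75 + 1) − 1.960) = Φ(2.472 − 1.960) = 69.6%.
- Events needed for 80% = (1.960 + 0.8416)² × (3.75/1.75)² = 36.04, so 37. Patients needed = 37 / 0.255 = about 145.

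**Step 5. Simulation of the planned type of test.** I used 20,000 trials with 55 per arm, constant hazards giving 36% and 15% by day 8, and 1% competing deaths. Patients who died stayed in the risk set, as in a subdistribution-hazard model. A two-sided 5% score test rejected in about 73% of trials (72.8% in one run, 73.2% in another). About 65 per arm were needed for 80%.

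**Step 6. Other two-sided checks at 55 per arm.**

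| Method | Power |
|---|---|
| Two proportions, unpooled variance | 74.0% |
| Two proportions, arcsine | 73.2% |
| Two proportions, pooled variance | 72.0% |
| Exponential hazards (Lachin) | 70.4% |
| Simple Wald approximation on the log HR, variance 1/19.8 + 1/8.25 | 68.5% |

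**Step 7. The effect that 110 patients can detect with 80% power.** By Schoenfeld at 28.05 events, HR = exp(2 × (1.960 + 0.8416)/√28.05) = 2.88. If the lower event count at a stronger effect is allowed for, HR 2.9 (preconditioning risk 14.3%, 27.6 events) gives 79.9%. In the simulation, with control risk held at 36%, power is about 76–77% at HR 2.9, about 79% at HR 3.0 and about 80% at HR 3.1.

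**The case against.** **The inputs are approximate.** Each planning risk is given as around a value, and small shifts move the answer. By Schoenfeld, 37% against 15% gives 79.8%, and 36% against 14% gives 81.2%. This stands as far as it goes: on that formula the gap lies within the uncertainty of the guesses. It does not rescue the statement, because those pairs imply hazard ratios of 2.84 and 2.96, while the article fixes 2.75 in two places. Freedman's formula gives only about 73–74% for the same pairs.

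**The formula is not shown and sidedness is not repeated beside the calculation.** This is true, and a condensed article may leave the formula out. Applying the two-sided statement to the sample size is a reading, but the natural one: it is the only sidedness given, and it is given for the study. The point is not that something is missing. The printed inputs and the printed result disagree under every two-sided method tried.

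**The shortfall is modest.** This is also true. It is under 4 percentage points by Schoenfeld and about 10 by Freedman. The endpoint, the test and the type I error are unaffected.

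**A stronger reading.** A reader might infer that a one-sided 5% level was used by mistake. One formula (Lachin, one-sided) does give 109.6 patients, close to 110. But other one-sided calculations give different answers: Schoenfeld power is 84.9%, and pooled proportions need 106 patients. One match among many combinations of formula and sidedness is weak evidence. The documents do not state the route, so this remains a possible explanation and should not be asserted.

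**Conclusion.** The 80% power stated in the abstract and the sample-size section does not follow from the article's own figures. With 28 expected events and a two-sided 5% test, power for HR 2.75 is about 70–76% depending on the method: Schoenfeld 76%, simulated Cox-type score test about 73%, Freedman about 70%. The type II error is therefore about 24–30%, not 20%.

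This assumes that the stated two-sided level governs the sample size, that the risks are exactly 36% and 15%, and that hazards are proportional. The simulation also assumes constant hazards over the 8 days. The 1% mortality makes almost no difference.

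Two further inferences would go too far. The trial need not enrol more patients, because an honest power figure is enough. Nor is 80% power assured from an HR of about 2.9, which holds by Schoenfeld only; the simulation puts it nearer 3.0–3.1.

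**What to change.** Restate the power in the abstract and in the sample-size section along these lines: *110 patients (55 per arm) give about 28 expected events and about 70–76% power (two-sided 5%) for a hazard ratio of 2.75 (36% against 15%); 80% power is reached at a hazard ratio of about 2.9 (Schoenfeld) to about 3.0–3.1 (simulation).*

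Name the formula or software and the sidedness used. Once the sponsor has settled on one method, the ranges can be replaced by that method's single figures. Keep the two-sided 5% test in the Statistical methods section.

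The cost is wording only. Enrolment, endpoint and analysis do not change, and the stated power becomes somewhat less favourable.
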